**ABSTRACT**

Introduction: Spondyloarthritis (SpA) is a rheumatic disease with either predominantly axial inflammatory symptoms of the spine and sacroiliac joints or predominantly peripheral arthritis. Extra-articular manifestations are associated with SpA. The most common manifestations are anterior uveitis, psoriasis and inflammatory bowel disease (IBD). Also cardiovascular disease (CVD) is frequently seen in patients with SpA, which is partly explained by systemic inflammatory activity, but the usual cardiovascular risk factors contribute as well. Peripheral arthritis occurs in approximately 30% of the patients, and shows an asymmetrical, oligoarticular pattern. Other common joint complaints are due to enthesitis, which manifest as extra-articular bony tenderness in areas such as the Achilles tendon, iliac crests and plantar fascia. Although less common, organ involvement in SpA can also be located in the heart, lungs, skin and kidneys. Overall it is important to realize that extra-articular manifestations frequently occur in patients with SpA and should be taken into account in the choice of treatment.

**Method and analysis:**

We anticipate that we will be able to enroll 100 adult individuals ( $\geq 18$  years of age) diagnosed with SpA. Among these individuals we want to explore the prevalence of concomitant extra articular manifestations. Data (duration of illness, diagnostic category, disease activity, extra-articular manifestations, blood, urine, and faeces samples, patient reported outcomes and comorbidity) will be collected from each participant. For all the clinical characteristics we will explore whether any of these have an impact on the reported disease activity according to the international standards – the Bath Ankylosing Spondylitis Disease Activity Index

**Ethics and dissemination:**

For the practitioner it is important to know whether certain co-morbidities have an impact on the disease activity, and subsequently to explore whether any of these could have prognostic value in a longitudinal study setting. The study will be approved by the ethics committee for the Region of Southern Denmark and the Data protection at Region of Southern Denmark. Dissemination will occur through presentations and publication in international peer-reviewed journals.

## INTRODUCTION

Spondyloarthropathies (SpA) is a heterogenous group of chronic rheumatic diseases with overlapping symptoms including psoriatic arthritis (PsA), ankylosing spondylitis (AS) arthritis associated with inflammatory bowel disease (enteropathic arthritis), reactive arthritis and undifferentiated SpA (1). SpA can be dominated by peripheral joint involvement, classified as peripheral SpA, or by inflammatory back pain, classified as axial SpA (ax-SpA). Furthermore ax-SpA is subdivided into two groups: Nonradiographic and radiographic. The Assessment of Spondyloarthritis International Society (ASAS) has made a set of criteria for recognizing patients with early ax-SpA to optimize treatment and to reduce the risk of irreversible joint damage. These criteria are summarized in **Figure 1**(2). It is estimated that peripheral arthritis occurs in around one third of the patients diagnosed with SpA, especially the large joints on the lower limbs are involved, often in an asymmetrical oligoarticular pattern (3). Furthermore enthesitis is a common manifestation in SpA. Next to the spinal and articular symptoms, many patients with SpA also have extra-articular manifestations which contribute to reduced quality of life (4). Recently, nephrolithiasis was identified as a common (up to 10%) and unrecognized extra-articular manifestation in AS (5). The etiology of SpA is complex and not fully understood. It is known that SpA is associated with multiple genes, such as HLA-B27 (6). However, the pathogenesis of SpA remains largely unknown. The complexity of the disorder indicates a multifactorial etiology involving multiple biological processes or pathways (7). Initially, SpA was considered a disease primarily of the male gender, but the profile has changed over time, and SpA has been regognized among females as well (8-10). Although specific cardiac manifestations as aortic valve disease or conduction disturbances is associated with SpA (especially AS), accelerated atherosclerosis also renders these patients more at risk cardiovascular disease. The cardiovascular risk factors and the systemic inflammation contribute to cardiovascular events (11, 12). Fecal calprotectin is a protein in neutrophil granulocytes and macrophages and is first found and described in 1980 (13) More and more studies focus on fecal calprotectin in IBD and confirm its value in

diagnosis, disease activity evaluation, effect evaluation, and relapse monitor (14) A prospective cohort study demonstrates that the sensitivity and specificity of CD are 100% and 97% (cutoff 30 mg/L) when compared to irritable bowel syndrome (IBS) (15) A strong link between AS and IBD is suggested. Recent studies found that 6.5% of patients with AS will develop IBD, and the prevalence of AS in patients with IBD is up to 10 % (16) Furthermore, even without clinical symptoms, up to 60 % of the patients with AS present gut inflammation at colonoscopy (17). Awareness of extra-articular manifestations among clinicians is important in view of their role in the diagnostic process, for treatment choices and for health related quality of life. The treatment of SpA aims to control the systemic inflammation and halt the progression of joint destruction and disability, and early treatment is important. Medical treatment in SpA spans from non steroidal anti inflammatory drug (NSAID), intraarticular corticosteroid injection to systemic treatment with synthetic Disease Modifying Anti-rheumatic drugs (DMARD) or biological treatment in terms of tumor necrosis factor inhibitors (TNFi) (3, 18)

### **Rationale and hypothesis**

In AS first line of therapy is NSAID, but in patients with simultaneous IBD these should be administered with caution as some studies have suggested that they exacerbate intestinal inflammation (19). Early induction of an anti-TNF therapy among these patients is recommended(20). Furthermore enthesitis is a typical feature in SpA and the treatment of these manifestations seem to be challenging as well. Studies have showed that anti-TNF therapy is superior to conventional DMARD in patients with longstanding enthesitis (21, 22). Uveitis is an acute inflammation of the uvea and is a common and potential serious extra-articular manifestation in patients with SpA. In most cases acute uveitis can be successfully treated by the ophthalmologists with local corticosteroids, but in some cases it develops into a refractory uveitis, and treatment with TNFi is recommended (as azathioprine and methotrexate do not have sufficient effect on the disease activity of SpA) (23, 24).

We anticipate that extra-articulare manifestations among patients with SpA is

underestimated and therefore undertreated, and contributes to a reduced quality of life. Spondyloarthritic disorders are generally diagnosed more often in men than in women (25). In reference to the most representative form of these disorders, ankylosing spondylitis, three male cases are documented for every female case (25). However, since the introduction of the new ASAS criteria for axial spondyloarthropathies these differences are no longer so apparent (26). SpA appears to be more frequent in men than in women, particularly in its axial presentations (27). Nevertheless, little is known of the differential clinical expression of SpA between males and females. The explanation for these differences is not clear, and the participation of multifactorial parameters cannot be discarded. A few studies have analysed gender as a prognostic factor of the SpA (8-10) and there is a need to determine the particularities and severity of SpA in the female gender. We hypothesise that the amount of self-reported disease activity is more pronounced in woman than in men. (i.e. Bath Ankylosing Spondylitis Disease Activity Index (BASDAI (28)) and Bath Ankylosing Spondylitis Functional Index (BASFI (29)). As it seems to be a link between IBD and SpA, we also aimed to measure faecal calprotectin in patients with any disease within the SpA spectrum.

## **Objectives**

The overall objective of this cross-sectional study is to perform a characterization of SpA patients, to identify clinical phenotypes of SpA and ultimately elucidate factors predictive of disease outcome. This insight will be important for rheumatologists in the perspective of making individualized treatment strategies, prognostic stratification and patient counseling.

## **Aims**

1. To analyze the distribution according to specific concomitant conditions in the SpA group:

Ankylosing spondylitis was diagnosed when the patients fulfilled the modified New York criteria (30), psoriatic arthritis was diagnosed when patients fulfilled the CASPAR criteria (31), enteropathic arthritis was diagnosed when patients exhibited inflammatory axial and/or peripheral

joint involvement associated to a confirmed IBD (Crohn's disease or ulcerative colitis), SpA was diagnosed when patients fulfilled the ASAS criteria (2), reactive arthritis was diagnosed when an asymmetric inflammatory oligoarthritis and/or inflammatory low back pain associated to confirmed genitourinary or gastrointestinal tract.

2. To characterize the extra-articular manifestations according to ASAS criteria, however also including the recently described nephrolithiasis among SpA patients:  
Anterior uveitis, (past or present), inflammatory bowel disease (past or present) enthesitis (past or present), psoriasis (past or present) dactylitis (past or present) and furthermore to assess other features as: urethritis, pyoderma gangrenosum, keratoderma blennorrhagica, erythema nodosum (past or present), nephrolithiasis (past or present), and urine components.
3. To estimate the male-to-female ratio among patients with SpA
4. To investigate faecal calprotectin in patients with any disease in the SpA spectrum
5. To analyze the influence of gender on self-reported disease activity:  
Estimation of disease activity and functional status is evaluated using BASDAI, BASFI and 36-Item Short-Form Health Survey (SF-36)
6. To analyze co-morbidity among SpA patients using Charlson Comorbidity Index

A priori hypotheses are as follows:

- A. The amount of self-reported disease activity is more pronounced in woman than in men

- B. Females are more likely to have peripheral joint involvement rather than axial compared to men
- C. Extra articular manifestations are more frequent seen in males compared with females
- D. Faecal calprotectin is higher in men than women
- E. Urine electrolytes are altered and related to nephrolithiasis and NSAID exposure

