## **METHODS**

### **Study design**

The study will be designed as a cross-sectional cohort design with prospective enrolment of patients with SpA over time. Information about the patients and their exposures will be collected at a single center at one visit (figure 2) according to the clinical standards in Denmark. Examinations will be carried out on the same day. Participant inclusion is expected to begin during 2016.

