### **Participants**

Patients with any disease of the SpA spectrum seen in the Department of Rheumatology, Odense University Hospital, Svendborg/Odense will be recruited. To be considered for inclusion, participants must have the ability and willingness to give written informed consent and to meet the requirements of this protocol. Participants must be at least 18 years of age. Participants will be excluded from the study if any of the following criteria are present: (1) no consent, (2) does not understand Danish, (3) age < 18 years.

All subjects will be informed about the project's purpose and content both oral and written - as per the Research Ethics Committee. Participants will receive information by MD [name]. Patients are made aware of the possibility to bring one accompanying person. The interview will take place in an undisturbed space at the rheumatology clinic. The subjects were informed that they could at any time withdraw their commitment to participate in the project, without this will affect the current or subsequent treatment or control. The subjects give permission to the investigator to have direct access to source data / documents (including DANBIO) for the monitoring, auditing and / or inspection

by the Research Ethics Committee or the Data Protection Agency. On the consent form, the investigator signing that written and oral information is given as above.

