### **Sample size considerations and statistical analyses**

This study is designed as an exploratory study. It is anticipated that 100 participants are likely to be included during a period of 6 months. A sample size of 100 individuals is considered sufficient to test the hypothesis: 'is there a difference between the reported BASDAI in SpA patients whether they are men or women? For a two-sample pooled t test of a normal mean difference with a two-sided significance level of 0.05, assuming a common standard deviation of 1.5 BASDAI units, a total sample size of 100 assuming a balanced design (1:1 male-female ratio) has a sufficient power (91%) to detect a mean difference of 1 BASDAI units.

All descriptive statistics and test will be reported in accordance with the recommendations of the "Enhancing the QUALity and Transparency Of health Research" (EQUATOR) network (36): the STROBE Statement (37). We consider p values less than 0.05 (and 95% confidence intervals excluding the null) to be statistically significant.

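### Aim 3 targets the sex ratio of SpA patients in general, but a sample of consenting attenders of one department yields a ratio that also depends on who attends and takes part

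*Protocol*

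**What the plan says.** Protocol, Aims, item 3: "To estimate the male-to-female ratio among patients with SpA". No source population or sampling frame is attached to the aim.

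The sample is described elsewhere:

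- Protocol, Participants: recruitment is of "Patients with any disease of the SpA spectrum seen in the Department of Rheumatology", and "participants must have the ability and willingness to give written informed consent". The exclusions are listed as "1) no consent, (2) does not understand Danish, (3) age < 18 years".
- Protocol, Study design: information "will be collected at a single center at one visit". Enrolment is prospective. Neither section states that patients are invited consecutively or that all eligible attenders are approached.
- Protocol, Sample size considerations and statistical analyses: "It is anticipated that 100 participants are likely to be included during a period of 6 months". The power for comparing BASDAI between men and women is calculated "assuming a balanced design (1:1 male-female ratio".

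The Rationale and hypothesis section gives the background on sex: three men to one woman in ankylosing spondylitis, a difference said to be less visible since the ASAS criteria, and SpA overall described as more frequent in men. It gives no figure for the whole SpA spectrum.

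**The concern.** The aim names a quantity that belongs to a disease population, while the data come from a selected part of one department's patients. For most aims of a descriptive study this is a general caveat. For a sex ratio it is more direct, because any difference between men and women in being invited, understanding Danish or agreeing to take part multiplies straight into the result. Taking part means an interview, a clinical examination, questionnaires, and blood, urine and stool samples, so equal willingness in both sexes cannot be taken for granted.

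The Rationale treats the sex balance of SpA as an unsettled question. A published ratio nearer to parity than the older 3:1 could be read as a change in the disease picture when part of it may be a difference in uptake. The information needed to tell these apart is the sex of eligible patients who were not enrolled. It is most easily captured during enrolment, and an analysis plan cannot create it from participants' data.

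**Working it through.** **Inputs.** From the protocol: N = 100, one department, consent required. For the power calculation: a two-sided 0.05 pooled t test, SD 1.5, difference 1 BASDAI unit, 50 men and 50 women, stated power 91%. Uptake rates by sex are not in the protocol; those used below are assumptions.

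**1. The plan's own figure.** Standard error = 1.5 × √(1/50 + 1/50) = 0.30. Noncentrality = 1 / 0.30 = 3.33 on 98 degrees of freedom. The noncentral t gives 91.0% power (normal approximation 91.5%). The stated 91% is reproduced.

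**2. Effect of uptake on the ratio.** Let R be the male-to-female ratio among the department's SpA patients, and let u_m and u_f be the proportions of men and women who end up enrolled. The expected ratio among participants is

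R × (u_m / u_f).

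With R = 2:

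| Uptake, men (assumed) | Uptake, women (assumed) | Ratio among participants |
|---|---|---|
| 50% | 50% | 2 × 0.50/0.50 = 2.00 |
| 50% | 60% | 2 × 0.50/0.60 = 1.67 |
| 60% | 80% | 2 × 0.60/0.80 = 1.50 |
| 50% | 70% | 2 × 0.50/0.70 = 1.43 |
| 60% | 50% | 2 × 0.60/0.50 = 2.40 |

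The shift can go either way and vanishes when uptake is equal. Only the quotient u_m / u_f matters, and it cannot be estimated from participants.

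**3. Sampling error at N = 100.** Exact (Clopper-Pearson) 95% limits for the male proportion p, converted to a ratio by p / (1 − p):

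| Men / women | 95% limits for p | Ratio (95% CI) |
|---|---|---|
| 50 / 50 | 0.398 to 0.602 | 1.0 (0.66 to 1.51) |
| 60 / 40 | 0.497 to 0.697 | 1.5 (0.99 to 2.30) |
| 67 / 33 | 0.569 to 0.761 | 2.03 (1.32 to 3.18) |
| 75 / 25 | 0.653 to 0.831 | 3.0 (1.89 to 4.92) |

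These intervals cover chance only and make no allowance for selection.

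**4. Does the 1:1 assumption interfere?** The 1:1 ratio enters only step 1. If the sample were 75/25, the same formula gives about 82% power instead of 91%. That is a consequence for the BASDAI comparison. It does not alter what Aim 3 estimates.

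**The case against.** The study calls itself exploratory, is openly single-centre, and attaches no hypothesis to Aim 3: the a priori hypotheses A to E do not include the sex ratio. Other aims use equally general wording and rest on the same sample. The uptake rates above are invented and their direction is unknown. The illustrated shifts, from 2:1 to between 1.4:1 and 2.4:1, all lie inside the chance interval for 67 men in 100 (1.32 to 3.18). If uptake is similar in both sexes, the participants do inform on the department's patients. All of this stands, and it keeps the point modest. It does not remove it, because the aim as worded still claims more than the sample can give, and selection error does not shrink with more participants.

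Two stronger readings are tempting, and the protocol does not support them.

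- A reader might infer that Aim 3 contradicts the balanced design. The section only computes power under 1:1, and no quota, matching or stratified enrolment by sex is stated. A study may plan power at 1:1 and still report the ratio it observes. Only an enforced balance would fix the answer in advance.
- A reader might infer that non-participants go uncounted. The participant-flow chart (Figure 2) could not be read in the text available, and its footnote lists lack of consent among the exclusions, so it may record those who declined. What can be said is that the readable text does not call for consecutive invitation.

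The remedy also has limits. A clinic list may not record language or classification criteria reliably, and a department count still carries referral effects. The Participants section describes access to records only as permission given by those enrolled.

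**Conclusion.** The point holds as a mismatch between the target of Aim 3 and its sample. The ratio among about 100 consenting, Danish-understanding attenders of one department reflects attendance and consent as well as disease, and the participants' data alone cannot correct it. The actual size is unknown. Under the assumed uptake rates a true 2:1 could appear as anything from about 1.4:1 to 2.4:1, with sampling error in addition. The conclusion that the aim is worded too widely does not depend on those rates, which only illustrate how far the ratio could move.

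The 91% power figure is correct under its stated assumptions, and the BASDAI comparison is not invalidated. The point is worth acting on because a numbered aim is affected, the remedy is cheap, and the tally is easiest to arrange before or during enrolment.

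**What to change.** 1. Reword Aim 3 so that it refers to adult SpA patients seen in the department during the enrolment period.
2. Compute the ratio, with a 95% confidence interval, from an anonymous count by sex of all such patients, taken from the clinic list or a screening log.
3. Report the participants' sex split beside it, as a check on participation.
4. If the tally is not feasible, restrict the aim to participants and say so.
5. Optionally, add one sentence to the sample-size section stating that no sex quota applies, if that is the intention. This only clarifies the phrase about a balanced design.

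The cost is a head count and a change of wording, with no extra visits or samples. The investigators should confirm that an anonymous count of patients who have not consented is covered by their approvals. Eligibility on a clinic list will be approximate, and the tally removes selection by consent but not by referral, so the result should be described as a department figure.

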### **Variables and outcome measures**

Included patients will undergo an examination programme to collect variables shown in **table 1**.

Informations on: (1) demographic data (age, sex, height, weight, educational level), (2) clinical characteristics (symptom duration, duration since SpA diagnosis, and type of the form of clinical involvement, HLA-B27, family history and extra-articular manifestations (3) activity data and monitoring methods (erythrocyte sedimentation rate (ESR), CRP, visual analogue scale (VAS) for pain and activity, morning stiffness, joint assessment, painful entheses [BASDAI]), (4) employment status and functional ability [BASFI]) and SF-36 (5) comorbidity will be obtained by interview.

The BASFI is a 10-item scale on which respondents rate the degree of difficulty they have in performing certain tasks, using visual analogue scales (VAS) from 0 (easy) to 100 (impossible). The mean of the 10 responses is the BASFI score. The BASDAI is a 6-item scale to measure severity of fatigue, spinal and peripheral joint pain, localized tenderness and morning stiffness, using the VAS scale as well. The Medical Outcomes Study SF-36 is a generic health status questionnaire that was developed as a tool to compare various aspects of health status across a general and broad patient population (32-34). The SF-36 examines eight general health domains: physical functioning, role limitations due to physical health problems, bodily pain, general health perceptions, vitality, social functioning, role limitations due to emotional problems and mental health. Furthermore, a physical and mental component summary score can be calculated. We will use the Danish version of SF-36 (35) which uses a 4-week recall period. For Peripheral articular involvement 44 tender/swollen joint count will be assessed.

**Table 1** Summary of measures to be collected

|                                                                      |   |
|----------------------------------------------------------------------|---|
| Demographics                                                  | X |
| Sex (M/F)                                                            | X |
| Age (year)                                                           | X |
| Height (cm)                                                          | X |
| Weight (Kg)                                                          | X |
| BMI (Kg/m  )                                             | X |

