| Disease Characteristics                                       |   |
| Symptom duration (months)                                            | X |
| Axial disease (yes/no)                                               | X |
| MRI positive (yes/no)                                                |   |
| Peripheral joint involvement (yes/no)                                | X |
| Medication                                                    |   |
| Prior NSAID (yes/no)                                                 | X |
| Current NSAID at assessment (yes/no)                                 | X |
| Prior DMARD therapy (yes/no)                                         | X |
| MTX dose (mg/week)                                                   | X |
| Other current DMARD therapy                                          | X |
| No. of previous biologics used (if any)                              | X |
| Name of current biological agent                                     | X |
| Dose of prednisolone orally at assessment (mg/week)                  | X |
| Intramuscular glucocorticoid injections in the previous 3 month (mg) | X |
| Clinical examination                                          |   |
| 46 swollen joint count                                               | X |
| 46 tender joint count                                                | X |
| BASMI                                                                | X |
| SpA features                                                  |   |
| Anterior uveitis, past or present (yes/no)                           | X |
| Inflammatory bowel disease, past or present (yes/no)                 | X |
| Psoriasis, past or present (yes/no)                                  | X |
| Preceding infection (yes/no)                                         | X |
| Total enthesitis count                                               | X |
| Dactylitis count                                                     | X |

|                                                                                                                                                                                                                   |   |
|-------------------------------------------------------------------------------------------------------------------------------------------------------------------------------------------------------------------|---|

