| Co-morbidities                                                                                                                                                                                             |   |
| Charlson Comorbidity Index                                                                                                                                                                                        | X |
| Urine sample                                                                                                                                                                                               | X |
| Basic metabolic screening                                                                                                                                                                                         | X |
| S-creatinin                                                                                                                                                                                                       | X |
| S-ioniseret calcium                                                                                                                                                                                               | X |
| S-urat                                                                                                                                                                                                            | X |
| Urine-pH (dip-stick)                                                                                                                                                                                              | X |
| Urine Calcium                                                                                                                                                                                                     | X |
| Urine Chloride                                                                                                                                                                                                    | X |
| Urine Potassium                                                                                                                                                                                                   | X |

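### Table 1 has no item for diuretics or calcium / vitamin D supplements, so Hypothesis E on urine electrolytes could not be adjusted for them

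*Protocol*

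**What the plan says.** Under Aims, the last of five a priori hypotheses (E) reads "Urine electrolytes are altered and related to nephrolithiasis and NSAID exposure". Variables and outcome measures ties data collection to Table 1: "Included patients will undergo an examination programme to collect variables shown in" that table.

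The Medication block of Table 1 covers:
- NSAIDs, prior and current, for example "Current NSAID at assessment (yes/no"
- DMARDs: prior use, methotrexate dose, and "Other current DMARD therapy"
- biologics: number used before, and "Name of current biological agent"
- glucocorticoids: weekly oral prednisolone dose, and "Intramuscular glucocorticoid injections in the previous 3 month (mg".

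There is no row for diuretics, for calcium or vitamin D supplements, or for other concomitant drugs. The narrative list of variables in the same section does not mention medication. The urine rows include calcium, chloride, potassium and sodium. The exclusion criteria under Participants are lack of consent, not understanding Danish and age under 18. The Introduction notes that "accelerated atherosclerosis also renders these patients more at risk cardiovascular disease".

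**The concern.** Hypothesis E is partly about what a drug does to urine chemistry, yet the drugs to be recorded are only those used to treat the rheumatic disease. Diuretics act on the renal handling of sodium, potassium, chloride and calcium. Calcium and vitamin D intake can change urine calcium. Given the cardiovascular burden that the Introduction describes, some diuretic use in this population is to be expected.

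Use need not be equal across the groups compared. Past stones count as cases (Aim 2), so some stone formers may be on preventive treatment when the urine is taken. Patients with heart or kidney disease may be on diuretics and also kept away from NSAIDs. Both are plausible assumptions; the protocol gives no figure for either. If they hold, part of an observed stone or NSAID difference would come from the co-medication. Information is collected at a single visit, so an analyst who later suspects this would have nothing to adjust for or to exclude on.

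**Working it through.** **The protocol's own figure.** The only stated calculation is the BASDAI comparison by sex: 50 versus 50, difference 1, SD 1.5, two-sided 0.05. The noncentrality is 1 / (1.5 × √(2/50)) = 3.33. With 98 degrees of freedom the power is 91.0%, which matches the stated 91%. This comparison does not involve urine and is unaffected.

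**What is and is not recorded.** Reading every row of Table 1 finds no item for the two drug classes. Possible substitutes:
- The Charlson index records diseases, not drugs.
- Blood vitamin D is measured, but is at best a partial proxy for one supplement.
- Access to source data, including DANBIO, is granted under Participants for monitoring, auditing and inspection. It is not a plan to record these drugs.

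**Size, under assumptions.** The documents give no rate of use and no drug effect, so these are assumed:
- effect of the drug on a urine analyte: 0.5 or 1 SD
- difference in use between the compared groups: 10, 20 or 30 percentage points
- stone contrast: 10 versus 90, from the Introduction's figure of up to 10% nephrolithiasis in ankylosing spondylitis applied to 100 patients
- NSAID contrast: 50 versus 50, an assumption without a source in the protocol.

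Spurious difference = drug effect × difference in use. The standard error in SD units is √(1/n₁ + 1/n₀), which is √(1/50 + 1/50) = 0.20 for 50 versus 50 and √(1/10 + 1/90) = 0.33 for 10 versus 90. The rejection rate with no true stone or NSAID effect is the two-sided tail of the noncentral t with 98 degrees of freedom and noncentrality equal to spurious difference / standard error.

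| Drug effect | Difference in use | Spurious difference | 50 v 50 | 10 v 90 |
|---|---|---|---|---|
| any | 0 points | 0 | 5.0% | 5.0% |
| 0.5 SD | 10 points | 0.05 SD | 5.7% | 5.3% |
| 0.5 SD | 20 points | 0.10 SD | 7.9% | 6.0% |
| 0.5 SD | 30 points | 0.15 SD | 11.5% | 7.3% |
| 1 SD | 10 points | 0.10 SD | 7.9% | 6.0% |
| 1 SD | 20 points | 0.20 SD | 16.8% | 9.1% |
| 1 SD | 30 points | 0.30 SD | 31.8% | 14.5% |

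**Check by simulation.** The formula treats the drug as a pure shift of the mean. A simulation (20,000 runs per scenario, use of 20%, 30% or 40% against 10%) also counts the extra variance from a mixture of users and non-users. At 1 SD and 40% against 10% it gives 28.0% for 50 versus 50 and 15.2% for 10 versus 90. With 10% use in both groups it gives 4.8% to 5.0%.

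**The case against.** **Table 1 is a summary.** It omits items that the protocol mentions elsewhere, such as educational level, employment status and family history, and it has no row for nephrolithiasis, one of the exposures in Hypothesis E. A missing row does not prove that a drug list will not be taken. This stands as a caution: the supported statement is that recording is not planned in the protocol. But nothing elsewhere in the protocol promises these drugs either.

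**The imbalance is assumed.** Without unequal use there is no bias, and the protocol links co-medication neither to stones nor to NSAIDs. This also stands. A reader might infer that Hypothesis E will be biased, or take 32% as the expected error rate. The documents do not support that: 32% needs a 1 SD effect, a 30-point difference in use, an even NSAID split and no added variance. Nor is the small stone group the more exposed contrast on these figures. A shift of 0.30 SD there is below its standard error of 0.33 SD.

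**Other drugs and analytes.** A reader might extend the point to urate-lowering drugs, because serum urate and "S-ioniseret calcium" are in Table 1. The hypothesis names urine electrolytes only. Those two measurements are in serum, urate is not an electrolyte, and there is no urine urate row. The extension does not hold.

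**The study is exploratory.** Hypothesis E is worded as an association, and unmeasured confounding is common to any one-visit cross-sectional study. This limits the weight of the point. It does not remove it, because the protocol applies p < 0.05 as its criterion for statistical significance, and the omission can be repaired only at data collection. The choice between adjusting and excluding can be left to an analysis plan. The collection of the variable cannot.

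**Conclusion.** The point holds as a gap in planned data collection. Diuretics and calcium or vitamin D supplements can alter measured urine electrolytes, are not planned to be recorded, and so could not be adjusted for in Hypothesis E. The size of any bias cannot be derived from the documents. Under the assumed effects of 0.5 to 1 SD and differences in use of 10 to 30 points, the false-positive rate is about 6% to 32% at 50 versus 50 (nearer 28% at the top if the added variance is counted) and about 5% to 15% at 10 versus 90. With balanced use it stays near 5%. This is a worthwhile low-cost improvement to one exploratory hypothesis, with no bearing on the sample size or on the BASDAI comparison.

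**What to change.** Add two rows to the Medication block of Table 1: Current diuretic (yes/no, agent) and Calcium / vitamin D supplement (yes/no). Report Hypothesis E with a sensitivity analysis that adjusts for users of these drugs or leaves them out.

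The cost is two more form items at a visit that already takes place. Leaving users out could noticeably shrink the stone group: if 3 of about 10 were users, 30% of it would be lost. Adjustment keeps those patients, but with so few stone formers it will be imprecise. Either result should be read as a check on the main finding.
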